**Secondary variables related to systemic metabolism:**

- Plasma glucose concentrations (mM);
- Plasma insulin concentrations (pM);
- Plasma HbA1c concentration (%);
- HOMA-IR score.

**Secondary variables related to changes in cerebral energy metabolism in a healthy control group matched by age and sex ([name] database):**

- Cerebral metabolic rate of glucose ( $\mu\text{mol}/100 \text{ g/min}$ ) quantified with 18F-FDG;
- Net glucose influx with 18F-FDG (Kglu; min);
- Cerebral metabolic rate of acetoacetate with 11C-AcAc ( $\mu\text{mol}/100 \text{ g/min}$ );
- Net acetoacetate influx with 18F-FDG (Kglu; min).

**Exploratory variables related to psychopathology and clinical status:**

- DUP;
- Medication lists and dose equivalence;
- Raw scores for various clinical questionnaires:
  - Clinical evaluation and symptoms: BPRS, CGI-S, ESS, BAS;
  - Depression: CDSS;
  - Functioning: GAF;
  - Cognition: BACS;
  - Medication: UKU, MARS;
  - Alcohol and drug consumption: AUDIT, DUDIT, FTND;
  - Physical activity: SIMPAQ.

**Exploratory variables related to metabolic and systemic changes:**

- Plasma concentrations of total ketones (mM);
- Plasma concentrations of triglycerides, total cholesterol, and free fatty acids (mM);
- Laboratory analysis parameters: Complete blood count, renal function (creatinine), liver function (AST, albumin), thyroid function (TSH), inflammation marker (C-reactive protein);
- Physical measurements (weight, height, waist circumference, blood pressure);
- Metabolomics;
- Cytokine and inflammatory profiles (plasma concentration).

**Secondary variables related to structural changes measured by MRI:**

- Global and regional brain volumes (ml);
- Cortical thickness (mm);
- Structural changes in brain vasculature (score).

**Exploratory variables related to continuous glucose monitoring:**

- Average glucose concentration;
- Standard deviation and coefficient of variation;
- Time in range.

## 9 Data Quality, Safety, and Monitoring

---

### 9.1 Good Clinical Practices

---

The study protocol and the management of the study's quality and safety are based on good clinical practices (GCP) and the institution's standard operating procedures (SOPs). The research staff are or will be trained on these standards before participating in the study.

### 9.2 Data Management and Validation

---

A data management procedure, including a system for double entry and data verification, has been established for this project to ensure that the data collected in the study are accurate and complete.

### 9.3 Quality, Safety, and Ethical Management

---

Deviations and violations of the protocol will be managed according to the institution's SOPs. The principal investigator is responsible for informing the Research Ethics Board (REB) in case of unplanned changes that could affect the integrity, dignity, or well-being of the participant, or that impact the ethical and scientific aspect of the project. Depending on the situation, corrective measures or a corrective action plan will be implemented.

Additionally, information on participant recruitment, compliance with inclusion/exclusion criteria, the consent process, dropouts, and compliance will be recorded and discussed throughout the study with the principal investigator and the qualified physician.

The goals are to:

- Evaluate whether the risks/benefits for the participant align with what was anticipated.
- Assess whether recruitment and dropout rates correspond to what was anticipated.
- Determine if protocol deviations require changes.
- Ensure that the protocol and ethical processes are respected.

## 10 Adverse Events Management

---

Since this project does not involve any interventions, adverse events that may occur during the study could only be related to the radiotracers. Follow-up will be conducted with the PET scan's responsible physician, Dr. [name].

Any adverse event occurring more than 24 hours after the radiotracer injection will not be considered related to the radiotracer or the study. Any side effects related to the APs will not be considered related to the project since they are prescribed with necessary medical follow-up by the treating team at the PEP clinic.

Adverse events will be managed and documented according to the institution's SOPs. Given the specific nature of the radiotracers and the clinical study, the following clarifications are to be considered when managing adverse events involving positron-emitting radiotracers:

- Medical conditions present before the injection of the radiotracers will not be considered adverse events.

- A deterioration of an evolving disease present before the radiotracer injection and not temporally related to the injection will not be considered an adverse event.
- Hospitalization or death due to the initial disease will not be reported as an adverse event.
- Injury related to poor intravenous catheter placement technique will not be considered an adverse event.

In the event of an adverse reaction to a radiotracer (Adverse Drug Reaction, ADR)—i.e., an adverse event for which there is a causal relationship—the CIMS adverse event form will be completed. If the event meets the criteria for rapid reporting—i.e., if there is a causal relationship with the radiotracer, and if it is serious and unexpected—it will also be reported to the CIUSSS de l’Estrie – CHUS REB and Health Canada’s Biologics and Radiopharmaceuticals Therapies Directorate according to current regulations.

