### Delayed Antipsychotic Administration

---

According to the guidelines of the National Institute for Health and Care Excellence (NICE Clinical Guideline CG 178) for psychosis and schizophrenia in adults: prevention and management, after the initial evaluation by the psychiatrist, 7 days are typically allowed before the initiation of medication to finalize the diagnosis with the treatment team and discuss treatment options with the patient and their family.

For this research project, the administration of antipsychotic medication (AP) may be delayed by an additional 2-3 days to perform the "BEFORE" imaging. The team will always aim to schedule

appointments within the 7-day period; however, if there are limitations (holidays, participant availability, equipment malfunctions, etc.), these additional 2-3 days will be considered while ensuring that the risk associated with this prescription delay remains minimal.

The risks associated with delaying the prescription of AP will be evaluated on a case-by-case basis in collaboration with the patients according to their clinical condition. Any patient who wishes for immediate AP prescription will receive it and will not be eligible for this research project. The majority of patients request additional time themselves to reflect and research the medications before receiving the prescription. Most request the medication introduction at the next appointment, 2 weeks later, and everything proceeds correctly without side effects, based on clinical experience related to the 2-week delay without AP.

The patient is free to change their mind during this period, either to accelerate the start of AP or to refuse AP altogether. In such cases, the patient will be excluded from the study. Additionally, as provided for in the usual care model of the PEP, the patient will be seen once or twice a week by their primary clinician from the PEP clinic for support and guidance towards non-pharmacological approaches for managing stress and psychotic symptoms. In case of an emergency, the patient is advised to contact their primary clinician. Should a change in health status occur during this period, appropriate medical follow-up will be conducted, and if the need for earlier medication initiation arises, the participant will simply be excluded from the study.

---

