### Blood Sampling

The risks associated with blood sampling and the installation of a glucose monitor are the same as those for all standard blood draws, including bleeding, bruising, discomfort, dizziness, pain at the sampling site, and the possibility of infection.

---

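### Section 10 allows only radiotracers to cause adverse events, but section 7.1 names other study-caused risks, including a delayed antipsychotic start; the two must be reconciled

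*Protocol*

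**What the plan says.** Section 10 of the protocol starts from the premise that the project involves no intervention and concludes that "adverse events that may occur during the study could only be related to the radiotracers". It then sets a time limit: "Any adverse event occurring more than 24 hours after the radiotracer injection will not be considered related to the radiotracer or the study". A bulleted list follows, introduced as clarifications for events that involve positron-emitting tracers. Two of its items are "A deterioration of an evolving disease present before the radiotracer injection and not temporally related to the injection will not be considered an adverse event" and "Hospitalization or death due to the initial disease will not be reported as an adverse event". A further item removes injury caused by poor technique in placing the intravenous catheter. Rapid reporting to the ethics board and Health Canada applies only where an event is serious, unexpected and causally linked to the radiotracer.

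Section 7.1 gives a different account of what the study can cause. Its first risk is the delay in starting treatment. The protocol says that "7 days are typically allowed before the initiation of medication", and that for this project "the administration of antipsychotic medication (AP) may be delayed by an additional 2-3 days". The next risk subsection opens with "The risks associated with blood sampling and the installation of a glucose monitor" and names bleeding, pain, dizziness and possible infection, among others. The MRI subsection names anxiety and panic attacks in claustrophobic people.

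**The concern.** Section 7.1 tells participants and the ethics board that taking part carries several risks unrelated to the tracers. Section 10 rules out in advance that any event could arise from them. Both cannot be right, and section 10 is the section that staff will follow when they classify an event.

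The delay matters most. Harm from it would appear as worsening psychosis, admission or, at worst, death, which are outcomes that section 10 treats as belonging to the underlying disease. If such an event is not classed as study-related, it does not meet the rapid-reporting rule. The pilot could then report no study-related harm from the delay simply because of how relatedness is defined. That would weaken the section 9.3 aim to "Evaluate whether the risks/benefits for the participant align with what was anticipated", and would leave whoever plans the next study without a usable account of this risk.

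**Working it through.** No sample size, power or error rate is involved. The check compares the two sections, with a little arithmetic on the schedule.

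**1. Is the delay part of the study?** Section 7.1 gives 7 days as the usual period before medication and an added 2-3 days for imaging: 7 + 2 = 9 and 7 + 3 = 10 days. Section 6.4 requires both BEFORE visits within 10 days of the first psychiatrist visit. The upper figure matches that limit, so the schedule makes room for the added days. Section 5.4 withdraws anyone who starts an antipsychotic before both BEFORE visits, apart from the permitted low-dose medication. Waiting until V2 is therefore a condition of staying in the study.

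**2. Which sentence of section 10 denies each risk?**

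| Risk named in 7.1 | When it can arise | Section 10 text that denies a link to the study |
|---|---|---|
| Antipsychotic delay, harm before V2 | Before any injection | Opening sentence only; the 24-hour rule does not reach it |
| Antipsychotic delay, harm appearing after V2 | May be more than 24 hours after injection | Opening sentence; 24-hour rule once the day has passed |
| Blood draw at V1 | Before any injection | Opening sentence |
| Blood draw at V3 | Weeks after the V2 injection | Opening sentence and 24-hour rule |
| Glucose sensor | Applied at the end of the imaging visit and worn for at least 8 days (sections 6.4, 6.6) | Opening sentence; 24-hour rule for nearly all of the wear |
| MRI anxiety or panic | At the scan, listed before the tracers in section 6.4 | Opening sentence |

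Every row is denied by the opening sentence. The 24-hour sentence adds to this because it excludes relatedness to the study as well as to the tracer. For example, an infected sensor site on day 5 is a risk that section 7.1 foresees and that section 10 declares unrelated to the study.

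**3. What happens to a participant who worsens before V2?** Under section 7.1, a participant who needs medication earlier receives follow-up and is excluded from the study. Section 5.1 plans for 18 participants to obtain 10 completers, that is 18 - 10 = 8 non-completers. An exit caused by deterioration during the wait would sit in that group, with nothing in section 10 to mark it as a possible effect of the study.

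**4. What could still bring it to light?** Section 10 says that adverse events are documented under institutional SOPs. Section 6.9 documents adverse events since the last visit when a participant withdraws. Section 9.3 reviews dropouts and the balance of risk and benefit, and has the principal investigator inform the ethics board of unplanned changes that affect well-being. These are real routes, but none of them says that harm from the delay or from a non-tracer procedure is to be assessed for relatedness.

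**The case against.** The best defence is that section 10 is a tracer-safety section written too broadly. The lead-in to its bullets limits them to events involving positron-emitting tracers. On that reading, the items on disease deterioration, hospitalisation, death and catheter technique only stop such events being logged as tracer reactions. This is a fair reading of the bullets. It does not rescue the opening sentence or the 24-hour sentence, which carry no such limit and are enough to create the contradiction.

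The delay is also short, conditional and supervised. Patients who want medication at once receive it and are not enrolled, clinic contact is once or twice a week, and section 7.1 says that most patients ask for more time themselves. That bears on how likely harm is, not on how it is classified.

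Safety is not a listed objective, and 18 participants say little about rare events: with none observed, the one-sided 95% upper bound is 1 - 0.05^(1/18), about 15%. This limits what the pilot can show, but it is no reason to classify events wrongly.

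A reader might infer more than the text supports:
- *That harm from the delay would never be recorded.* The SOP sentence, the withdrawal provision and the section 9.3 review leave indirect routes open, and the SOPs are not shown.
- *That all catheter injury is excluded.* Only injury from poor placement technique is.
- *That two 24-hour windows, set against 5 to 7 weeks of participation, give the share of harm captured.* That ratio measures calendar time rather than risk, and it treats attribution as if it were recording.

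**Conclusion.** The contradiction is on the face of the protocol. Section 10 recognises one source of study-related harm. Section 7.1 names at least three others: the treatment delay, blood sampling with sensor placement, and the MRI. If section 10 is followed as written, harm from these would not be classed as study-related and would fall outside rapid reporting. Deterioration before V2 would show mainly as an exclusion.

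The effect is on classification and reporting, and the documents give no basis for estimating how many events would be affected. The conclusion assumes that no institutional SOP overrides the explicit text of section 10. It takes no position on the length of the delay or on when treatment should start. The point is worth correcting before enrolment because it concerns participant safety in a group whom section 7.4 describes as potentially more vulnerable.

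**What to change.** Reconcile section 10 with section 7.1:

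1. Delete the statement that only radiotracers can be the cause, and remove the words *or the study* from the 24-hour sentence.
2. State that the 24-hour rule and the bulleted exclusions (disease deterioration, hospitalisation or death, catheter placement technique) decide radiotracer causality only.
3. Record adverse events from consent onward, including worsening, hospitalisation, death and early exit before the first antipsychotic dose, as well as events from blood draws, the sensor and the MRI.
4. Assess relatedness to study procedures, including the delay, case by case.
5. Tabulate these events, including for participants withdrawn before V2, so that the section 9.3 review has data to work from.

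The cost is a rewording of one section, some added recording and a few more reports to assess. Existing clinic contact once or twice a week already offers the occasion to collect the information. Treatment and visit timing are unchanged.

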### PET Scan Procedure

---

Two intravenous catheters will be placed in the forearms, and blood glucose will be measured.

- Approximately 15 minutes before the radiotracer injection, the participant will be encouraged to lie down on the examination gurney or on a gurney in a room adjacent to the examination room.
- CT scan will be performed for a few minutes before the PET scan acquisition begins.
- The radiotracer, adjusted to a volume of 5 to 10 ml of saline (NaCl 0.9%), will be injected through one of the catheters.
  - 11C-Acetoacetate:370 MBq (10 mCi)
  - 18F-FDG:185 MBq (5 mCi)
- The PET scan will last 20 to 30 minutes (depending on the radiotracer).
- Repeated blood samples will be taken during the various PET scan acquisitions (10 ml per PET scan) through one of the catheters.
- Since two radiotracers are used during a single imaging session, there will be a 15 to 30-minute break; the participant will be invited to get up, walk around, and use the restroom.
- After the imaging session, the participant's overall health will be checked, and a snack will be provided.

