## 6.9 Participant Withdrawal

---

When the participant stops or is withdrawn from the study, no further data collection or final visit will occur except to document any adverse events that have occurred since the last visit or follow up with the participant to remove the continuous glucose monitor. All data and samples collected until the participant's withdrawal will be retained per applicable standards.

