### MRI

Magnetic resonance imaging (MRI) is completely painless. It is a radiation-free examination. No particular consequences for humans have been described. The only risks are related to implanted pacemakers, heart valves, or any unreported metallic foreign bodies. A detailed and standardized questionnaire is conducted by the technologist to ensure the absence of metallic bodies. Claustrophobic individuals may feel uncomfortable, experience anxiety, or have a panic attack.

---

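### Section 10 treats radiotracers as the only source of study adverse events, against the procedure risks listed in section 7.1, so procedure harm would be under-counted and misattributed

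*Protocol*

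**What the plan says.** Section 10 starts from the premise that the project has no intervention, and concludes that "adverse events that may occur during the study could only be related to the radiotracers". It then sets a time limit: "Any adverse event occurring more than 24 hours after the radiotracer injection will not be considered related to the radiotracer or the study".

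A list follows, introduced by the words "the following clarifications are to be considered when managing adverse events involving positron-emitting radiotracers". One item says that conditions already present before the injection are not adverse events. Another says: "Injury related to poor intravenous catheter placement technique will not be considered an adverse event". The only form the section names (CIMS) is for a radiotracer reaction, and its expedited reporting route requires a causal link to the radiotracer. The section also says, in general terms, that adverse events are handled and documented under institutional SOPs.

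Section 7.1 describes risks from other sources. Under Blood Sampling: "The risks associated with blood sampling and the installation of a glucose monitor are the same as those for all standard blood draws", followed by a list that includes bleeding, bruising, dizziness, pain and infection. Under MRI: "Claustrophobic individuals may feel uncomfortable, experience anxiety, or have a panic attack". Section 6.6 makes catheters part of each PET session: "Two intravenous catheters will be placed in the forearms, and blood glucose will be measured".

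**The concern.** The catheters, the V1 and V3 study draws, the sensor and the MRI are all research procedures. Section 7.1 tells the ethics board that they carry risk. Section 10 says that only the radiotracers can cause an adverse event. Both cannot be right.

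This is more than missing detail, because section 10 states rules that decide how an event is classified. One rule says a particular injury is not an adverse event. Another says that a late event is unrelated to the study. An infected sensor site on day 5 would fall under the second rule.

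What is at stake is the pilot's account of how well its procedures are tolerated. The study is meant to prepare later ones, and section 4 includes the acceptability and feasibility of glucose monitoring among its exploratory objectives. Section 9.3 also plans to compare risks with what was anticipated, and that comparison needs procedure events to be counted and attributed correctly. The primary PET objective is not affected.

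**Working it through.** The protocol gives no figure for procedure events, so there is none to reproduce. The check applies section 10's rules to the schedule in sections 6.3, 6.4 and 6.6.

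**Inputs**
- Attribution window: 24 hours after injection (section 10).
- Sensor: applied at the end of the imaging visit and removed after 8 to 10 days (section 6.4). Section 6.6 gives 8 to 12 days.
- V1 and V2 come before the antipsychotic starts; V3 and V4 come 4 to 6 weeks after it starts (section 6.4).
- Order within an imaging visit as listed in section 6.4: MRI, catheters, first tracer, break, second tracer.

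Section 6.6 places the sensor at a metabolic visit, a term the schedule does not define. I follow section 6.4 and Table 1, which tie it to the imaging visit.

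**Sensor.** It goes on after the last injection, so less than one full day of wear can fall inside the window. The share of wear outside is therefore at least (days worn − 1) / days worn:
- 8 days: 7/8 = 87.5%
- 10 days: 9/10 = 90%
- 12 days: 11/12 = 91.7%

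This is a share of wear time, not of events. Bleeding at insertion would fall inside the window; an infection could well appear after it.

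**V3 blood draw.** V2 precedes the start of treatment and V3 follows it by at least 4 weeks. The gap is therefore at least 4 × 7 = 28 days, against a window of 1 day. Taking V3 before V4, as numbered, an injury from this draw is by rule not related to the study.

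**V1 blood draw and MRI.** V1 precedes any injection. The MRI is listed before the catheters and injections, although section 6.5 allows it at a separate visit. Read literally, the pre-injection rule could exclude a bruise from V1 or a panic attack in the scanner.

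**Catheters.** Injury from poor technique is excluded by definition, whatever its timing. Injury after competent placement is not covered by that item.

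**Inside the window.** An event in the first 24 hours escapes the time limit, but it still meets the opening premise that only a radiotracer can be the cause.

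| Source of event | Stated rule in section 10 that applies | Effect |
|---|---|---|
| Catheter, poor technique | Technique item | Not an adverse event |
| Sensor, after day 1 | 24-hour rule | Not study-related |
| V3 draw | 24-hour rule | Not study-related |
| V1 draw; MRI before injection | Pre-injection item, read literally | Not an adverse event |
| Sensor, first day | Radiotracer-only premise | No procedure category |

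**The case against.** A reader might infer that section 10 rules out all catheter injury, leaves nowhere to record other procedure events, and so guarantees a count of zero. The documents do not support that, for four reasons.

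- The catheter item covers only poor technique. A haematoma or infection after correct placement is outside it. Section 7.1 does not name catheter placement among its risks either, so that item alone does not directly contradict it.
- The list is framed as clarifications for radiotracer events. It can be read as separating technique injuries from tracer reactions, not as a study-wide definition.
- Section 10 sends adverse events to institutional SOPs, which are not shown, and section 9.1 ties safety management to GCP. Procedure events may well be documented there.
- Section 6.9 documents adverse events of any kind at withdrawal, next to the provision to "follow up with the participant to remove the continuous glucose monitor".

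It is also fair to say that nothing makes sensor acceptability depend on adverse-event counts, so that objective can still be assessed.

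These points remove the claim of zero, but not the contradiction. The radiotracer-only sentence and the 24-hour rule stand outside the list, so the list's framing does not limit them. The 24-hour rule expressly denies a link to the study as well as to the tracer. Documentation under SOPs does not change that attribution, and an injury defined as not an adverse event may never reach the SOPs. Section 6.9 applies only to participants who leave.

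**Conclusion.** The concern holds as a contradiction between sections 7.1 and 10 that would under-count and misattribute procedure harm. Injury from poor catheter technique would not count as an adverse event. At least 87.5% of sensor wear time, and the whole of the V3 draw, fall where section 10 declares events unrelated to the study.

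The number of events affected cannot be derived, because the protocol gives no event rate for any of these procedures. Most would probably be minor, in a pilot that enrols 18 to obtain 10 completers. The conclusion assumes that section 10 is applied as worded, that the visits run in their numbered order, and that the sensor is placed at the imaging visit. How much is still documented depends on the SOPs. The point is worth correcting for safety reporting, but does not threaten the primary analysis.

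**What to change.** Reconcile sections 7.1 and 10:

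1. Replace the radiotracer-only sentence with one that recognises both radiotracers and study procedures as possible causes.
2. Delete the catheter-technique item, or limit it to saying that such an injury is not attributed to the radiotracer.
3. Limit the 24-hour and pre-injection rules to radiotracer causality, and remove the reference to the study from the former.
4. State that an event arising from a study catheter, blood draw, glucose sensor or MRI is recorded as related to a study procedure, through sensor removal, and tabulated separately from radiotracer reactions.
5. Keep the CIMS form and the Health Canada route for radiotracer reactions.

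Steps 1 and 3 are needed as well as step 2. Recording events through sensor removal would otherwise contradict a 24-hour rule left unchanged, since the sensor is worn for at least 8 days.

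The cost is a few sentences in section 10 and a line on the adverse-event form. A few more minor events will be recorded, so the safety table will look slightly less favourable.
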